### Economic evaluation

To analyze cost-effectiveness, we will focus on the results of the program defined as reduction of complications, improving survival, less need for postoperative care and improvements in social productivity. The economic evaluation will be performed per participating center and includes incremental cost-effectiveness and cost-utility analysis using the RAND and iMTA-PCQ questionnaires. The cost-effectiveness ratio will be calculated by dividing the difference between the mean total costs for the exercise and control groups by the difference in the mean effect in the groups [41]. The cost-utility ratio expresses the additional costs of the intervention compared with the control group per quality-adjusted life years [42].

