All secondary outcomes will be described as means plus SD or median plus IQR, with the data being continuous, and measures for each time point being normally and non-normally distributed respectively. Categorical parameters will be described as number plus percentage per time point. Statistical methods will include t-test and the Mann-Whitney U test for continuous parameters, distributed either normally or not normally respectively, at a single postoperative time-point. Categorical outcomes will be analyzed with Chi-square testing or regression analysis (logistic, ordinal or nominal, depending on the definition of the parameter) for single time points. The size of the sample will be calculated on the basis of the primary aim: the reduction of postoperative complications as determined with the CCI score. With our population variables, the CCI mean is 10.4 (SD 14), and the target reduction is 30%. We use an alpha of 0.05 and power of 0.80 (two-sided test). We expect a dropout rate of 10%. We therefore need 714 patients: 357 in each arm. This gives us sufficient statistical power to demonstrate the expected proportion of difference (55% versus 20%) in the 6MWT between baseline and surgery based on previous studies [14, 27]. Approximately 600 eligible CRC patients undergo surgery in one of the six participating hospitals annually. This implies that we will complete inclusion within two years with the inclusion period being followed by a year of follow-up.

Due to limited clinical data regarding effect size of the primary endpoint – CCI - an interim analysis will be performed. The interim analysis is planned if half of the intended number of subjects have completed the 4 week assessment (i.e. timing of the primary endpoint assessment). The intention of the interim analysis is to terminate the study if there is a statistical significant difference between study arms.

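### The economic evaluation is specified per participating centre with no pooled analysis stated, which would leave each centre's ratio too imprecise to support a conclusion

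*Protocol article*

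**What the plan says.** The Economic evaluation section of the protocol article sets the level of the analysis: "The economic evaluation will be performed per participating center and includes incremental cost-effectiveness and cost-utility analysis". It defines the cost-effectiveness ratio as obtained "by dividing the difference between the mean total costs for the exercise and control groups by the difference in the mean effect in the groups". For the effects it says "we will focus on the results of the program defined as reduction of complications, improving survival, less need for postoperative care", and it adds social productivity; the cost-utility ratio uses quality-adjusted life years (QALYs). It does not say which of these effects forms the denominator of the cost-effectiveness ratio.

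The Statistical analysis section gives the number of centres: "Approximately 600 eligible CRC patients undergo surgery in one of the six participating hospitals annually". It sizes the trial on CCI for one comparison of the two arms over all centres, with 714 patients, 357 per arm. The Randomization section stratifies by study site. Cost-effectiveness is listed as a secondary outcome in the abstract, under Study objectives and under Study outcomes.

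**The concern.** An incremental ratio is usable only if its denominator is reasonably well separated from zero. The trial has about 80% power for the CCI difference when all centres are combined. Dividing the patients by six multiplies the standard error of that difference by about √6 ≈ 2.4, so a denominator that is secure in the pooled data becomes fragile in each centre.

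A wrong-sign denominator does more than widen an interval: it reverses the meaning of the ratio. The Discussion expects lower health expenditure, so cost differences may well be negative. A negative ratio can then mean either cheaper and better or dearer and worse, and the ratio alone does not tell these apart.

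The plan would thus yield at least six cost-effectiveness ratios and six cost-utility ratios, and no stated overall answer. The limitations paragraph of the Discussion says the international design is meant to show that worldwide implementation may be possible, which calls for a trial-wide estimate.

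**Working it through.** **Inputs from the protocol (Statistical analysis section)**
- "the CCI mean is 10.4 (SD 14), and the target reduction is 30"%: planned difference 0.30 × 10.4 = 3.12 points.
- "We use an alpha of 0.05 and power of 0.80 (two-sided test").
- "We expect a dropout rate of 10"%.
- 357 per arm, six hospitals.

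**Assumptions the protocol does not supply**
- Recruitment is equal over centres (varied below).
- CCI is the effect in the denominator.
- The true effect is the same in every centre.

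**1. The plan's own sample size.** n per arm = 2(1.960 + 0.842)² × 14² / 3.12², which rounds up to 317. Allowing for dropout, 317/0.9 rounds up to 353 per arm, 706 in total. The exact t calculation gives 318, then 354 per arm, 708 in total. Both are close to the stated 357 and 714, so the inputs are being read as the protocol meant them.

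**2. Evaluable patients.** 357 × 0.9 = 321.3 per arm. Divided by six, this is 53.55, about 54 per arm per centre.

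**3. Precision and sign of the effect difference.** SE = 14√(2/n); P(wrong sign) = Φ(−3.12/SE).

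| | Pooled | One centre |
|---|---|---|
| n per arm | 321 | 54 |
| SE | 1.10 | 2.71 |
| 95% half-width | 2.17 | 5.30 |
| Power | 81% | 21% |
| P(wrong sign) | 0.2% | 12.4% |

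In a single centre the half-width exceeds the planned effect. In about 79% of such analyses (100% − 21%) the 95% interval for the denominator would include zero.

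**4. All six centres.** P(at least one wrong sign) = 1 − (1 − 0.1244)⁶ = 0.55. The expected number is 6 × 0.1244 = 0.75.

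**5. Sensitivity to the assumptions**
- *Half the planned effect (1.56 points):* 28% per centre, 86% for at least one of six.
- *Unequal recruitment:* two assumed splits were tried, with shares of 30/25/15/12/10/8% and 40/20/15/10/10/5%. Centre sizes then run from 128 down to 16 per arm. The chance of a wrong sign is 4% in the largest centre and 26% in the smallest; for at least one of six it is 60% and 64% respectively.
- *Skewed CCI with many zeros:* simulated with 50% zeros in the control arm, 65% in the intervention arm and gamma-distributed positive scores, with 54 per arm. The chance is about 11% per centre.

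No corresponding figure can be computed for the cost-utility ratio, because the protocol gives neither an SD nor an expected difference for QALYs.

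**The case against.** The strongest reply is about reading. The definition of the ratio is in the singular and refers to the two trial groups; a cost-effectiveness analysis is listed once as a secondary outcome; and the Statistical analysis section promises a comparison of the arms on primary and secondary outcomes. On this view the centre wording may refer only to local costing within a trial-wide comparison. That is possible, but the sentence attaches the centre level to the evaluation that contains the ratios, and no section says that a pooled ratio will be formed. If costing was the intention, the sentence still needs correcting.

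There is also a rationale for centre-level results. The Discussion notes differences between countries in circumstances and facilities, and stratification by site makes within-centre comparisons valid. This stands, and is a reason to keep centre-level results as secondary. Differences in prices can be handled through unit costs without splitting the effect estimate.

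Three stronger readings are tempting, and the document does not support them:
- *All six ratios would be uninterpretable.* A 12% chance per centre means fewer than one wrong sign expected in six, and a 45% chance of none. A wrong-sign estimate can also be reported as a position on the cost-effectiveness plane with its uncertainty.
- *The sponsor has excluded a pooled analysis.* The article omits one and nowhere rules it out.
- *The economic methods are deficient because resampling, acceptability curves and sources of unit costs are not described.* A protocol article ordinarily leaves these to the full protocol or analysis plan.

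**Conclusion.** The point holds in a limited form. The article makes a positive choice of analysis level that does not suit the size of the trial, and an analysis plan that follows it would inherit the problem. Even if prehabilitation works exactly as planned, a typical centre would have about 21% power on the effect, and it is slightly more likely than not (55%) that at least one of six would show the effect in the wrong direction by chance. The per-centre ratios would be too imprecise to support a conclusion and could conflict in sign.

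The percentages rest on CCI as the denominator, the full planned effect in every centre, and equal recruitment. Under the unequal splits examined, the smaller centres do worse and the chance of at least one wrong sign rises. The finding concerns a secondary outcome: the sample size and the primary analyses are unaffected, and no new data would be needed to correct it.

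**What to change.** Reword the Economic evaluation section, and any analysis plan that follows it, to say that:
- the main economic analysis is the pooled intention-to-treat comparison over all centres, for both the cost-effectiveness and the cost-utility ratio;
- centre- or country-specific unit costs are applied to each patient's resource use, and centre enters as a covariate, in line with the site-stratified randomisation;
- per-centre costs and effects are secondary or descriptive.

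If centre-specific costing within a pooled comparison was the intention all along, one sentence saying so is enough. The cost is a change of wording. The small downside is that the main ratios are less specific to each locality, which the centre-level tables largely make up for.

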## Discussion

Despite advances in surgical techniques and improvements in postoperative care, morbidity and mortality remain high in CRC patients undergoing surgery. Postoperative complications occur in up to 50% of patients and surgery is associated with a 20 to 40% reduction in physiological and functional capacity [2–5].

Since we know that the number and severity of complications are, or may be, associated with preoperative functional capacity, nutritional status, smoking behavior and psychological well-being, it is incumbent on us to test a multimodal intervention program that targets these issues. Traditional approaches have focused on the postoperative period for rehabilitation and lifestyle changes. However, recent evidence has shown that the preoperative period is a better time to intervene [27]. Therefore, we initiated the first international randomized controlled trial on multimodal prehabilitation for patients undergoing colorectal surgery for cancer.

Patient lifestyle (stated as inactivity, obesity, dietary pattern, and smoking behavior) is an important contributor to the development of CRC [43]. Moreover, CRC patients often develop problems with their nutritional status which may aggravate deconditioning and muscle wasting (sarcopenia) [31, 32, 44]. This implies that, particularly in this group of patients, there is considerable potential for improvement in both nutritional status and functional exercise capacity [45–47]. A recent review indicated that optimizing functional exercise capacity in the surgical population can, by comparison with controls, result in fewer postoperative complications, shorten the length of hospital stay, reduce disability, and improve quality of life [48]. However, there have been no previous studies rigorously evaluating the impact of multimodal prehabilitation prior to digestive surgery.

Interventions that involve physical exercise training for endurance and strength, nutrition, mental support and smoking behavior have all found an independent and clinically relevant effect on the reduction of postoperative complications in small studies. If all these interventions are orchestrated in an innovative prehabilitation program, it may prove feasible to design a highly effective and comprehensive intervention. Synergy may result from these individual interventions if they are applied in a multimodal program since it is known that protein supplements one hour after exercise improve uptake and enhance anabolic effects [30–33, 44, 49]. Nutritional supplementation four weeks before and after surgery has been shown to enhance preoperative functional walking capacity and recovery in patients undergoing colorectal resection for cancer [34]. Moreover, the release of dopamine during exercise improves the psychological mindset and smoking cessation improves the ability to perform exercise.

After the diagnosis of CRC, there is a relatively short period of 4–5 weeks before the actual surgery. A rigorous intervention program of prehabilitation is therefore required that is closely coordinated with the entire medical treatment program. An additional potential benefit is the empowerment of patients, who may then play an active role in coping with their disease. From a physiological point of view and based on limited practical experience, it seems feasible to achieve clinical relevant effects during the period of four weeks between diagnosis and surgery. However, this is possible only with a combination of robust innovative interventions involving nutrition, physiological support, smoking cessation and exercise training. These ideas are supported by Carli et al., who stated that a multidisciplinary prehabilitation program needs to be developed, tested, implemented and delivered to patients [16, 35].

Another reason why optimal recovery after surgery is important is because it will increase the potential of patients to withstand additional therapies such as chemotherapy, targeted immunotherapy, metastatic disease resection and/or hyperthermic intraperitoneal chemotherapy (HIPEC) [50, 51]. A study by the Dutch cancer register included 11.000 stage-3 CRC patients (2008–2013) [7]. 4899 of whom were not treated with chemotherapy. The five-year survival rate in this group was only 39%. If chemotherapy started > 12 weeks postoperatively, the five-year survival rate increased to 54%. When chemotherapy began < 6 weeks after the operation, this rate increased further to 76%. Improved functional capacity may facilitate an earlier start of adjuvant chemotherapy and thereby increasing survival an improving HRQoL [7, 8, 52, 53].

Despite previous evidence from small-scale trials, there are currently no standardized prehabilitation programs and they are therefore not mentioned in current medical guidelines. This highlights the need to design, test, optimize, and implement a multimodal program for maximizing improvements in nutritional status and functional capacity prior to surgery. We expect to see a reduction in postoperative complications, Length Of hospital Stay (LOS), intensive care stay, 30-day mortality rate, and health expenditure due to the multimodal prehabilitation program. The sum of all these separate outcomes will be measured using the Comprehensive Complication Index (CCI), which is a relatively new and interesting outcome measure [40]. As stated in the literature, patients with postoperative complications report a lower HRQoL than patients without. We will be the first to determine whether the HRQoL of patients with postoperative complications is inferior both preoperatively and 1 year postoperatively than the HRQoL of patients without complications. We expect poorer HRQoL in patients with complications preoperatively and one year postoperatively than in patients without complications.

Limitations of the study should be noted as well. Due to its nature this study is performed non-blinded. This may result in higher dropout rates or an increased activity level in the control group, due to the growing and intuitive understanding of the benefits of exercise training and optimal nutrition. To limit this potential bias of increased activity, we will introduce activity trackers to all patients. We do realize patient characteristics, social circumstances and healthcare facilities will not be the same in all countries. Therefore, we will stratify per participating center. Our international approach of the randomized controlled trial will demonstrate that a worldwide implementation may be possible. In case our multimodal program proves to enhance postoperative outcome, it will be impossible to discover which element of the program attributed most. A large sample size and different outcome measurement will facilitate subgroup analyses, to determine effects of the program within different areas, such as functional capacity, body composition, and quality of life. Also, to allow for comparison of the effects of single modal interventions in this multimodal program. Our large sample size will also give us the possibility to analyze the possible effect differences of an intensive hospital-based prehabilitation program in different patient groups. This way, prehabilitation in the current form can be implemented for patient groups who will benefit the most from intensive hospital-based training. For less high-risk patients, future research could focus on programs in which training is less intensively monitored, such as home-based programs.

Our study investigating prehabilitation is a good example of research in prevention and it will be the first to systematically implement existing knowledge from a variety of different medical specialties and basic science into a four-element multimodal preoperative program for CRC patients with the aim of improving functional capacity and reducing the postoperative complication rate.

## Abbreviations

6-MWT: Six minute walk test
CAL: Colorectal anastomotic leakage
CCI: Comprehensive complication index
CHAMPS: Community health activities model program for seniors
CPET: CardioPulmonary exercise testing
CRC: ColoRectal cancer
DSMB: Data safety monitoring board
ERAS: Enhanced recovery after surgery
GAD-7: Generalized anxiety disorder 7
HIPEC: Hyperthermic intraPEritoneal chemotherapy
HIT: High intensity training
HRQoL: Health related quality of life
LOS: Length of hospital stay
MMC: Máxima medical center
NRT: Nicotine replacement therapy
PG-SGA: Patient generated subjective global assessment
PHQ-9: Patient health questionnaire 9
SD: Standard deviation
